### Salivary cortisol

Saliva samples will be collected using salivettes with an insert containing a sterile polyester swab, yielding a clear and particle-free sample. They will be used according to the manufacturer’s instructions (Sarstedt G & Co, Numbrecht, Germany). The salivettes will be centrifuged at 500 rpm for 2 hours, and the filtrates will be stored frozen (−20C) until analysis, which will be performed with standard ELISA kits from Enzo Life Sciences Inc, New York, USA. The samples will be thawed and individually recentrifuged before the analysis.

### Statistical analyses

Sample size was calculated using G*Power 3.1 software.^38^ Since this is an original study and no a-priori power analysis is provided, we estimate a moderate *f* – size effect (0.25). The analysis considered four groups, 4 measurements, correlation between repeated measures of 0.5, alpha of 0.05 and power of 0.85, resulting in a sample size of 28 participants. Considering possible losses, we estimate recruitment of 30 subjects (120 observations).

The Shapiro-Wilk test will be applied to identify the sample distribution. Assuming a normal sample, we will perform analysis of variance (ANOVA) having ‘group’ as independent variable and ‘area of activation’ (observed in the left DLPFC) as dependent variable. The Kruskal-Wallis test will be performed in case of a non-parametric sample. The SPECT images will be available in orthogonal cuts in the transverse, sagittal, and coronal planes (DICOM format). Images will be analyzed using the Statistical Parametric Mapping software (SPM12; Wellcome Department of Imaging Neuroscience, London, UK), executed in Matlab Version 2020 (MathWorks, Natick, MA). We will use SPM to form a statistical map according to the statistical threshold to identify differences among the groups. In-house scripts will be used for partial volume correction procedures based on structural MRI. The SPM images will be subtracted from each group to verify areas of functional activation.

ANOVA or its non-parametric extension will be applied for n-back and salivary cortisol, with ‘group’ as independent variable for both outcomes and ‘cortisol level’ (for salivary cortisol) and accuracy/response time (for working memory performance) as ‘dependent variables’. The associations between n-back task performance (accuracy and response time)/salivary cortisol level and cerebral activation will be estimated with linear regression. We will perform pathway analyses to verify whether cerebral activation is directly associated with the results of working memory performance and cortisol salivary level or is measured by these findings. We will also statistically investigate the possible learning effects of the repetitive application of the working memory task by grouping participants’ scores according to the chronological order of NIBS intervention assignments.

The mood scales administered before each NIBS session (such as HAMD, BDI, PANAS, and HAI) will be used to investigate major mood oscillation between sessions. If significant mood changes (p < 0.05) are found, we will use these measures as potential moderators of the main outcomes of this study. Moreover, the VAS will be used to investigate any significant change in pain intensity before and after each session as well as between NIBS sessions. Finally, ANOVA will also be applied to investigate adverse effects (dependent variable) across groups (independent variable).

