**Objective:**

We propose to investigate the combined and standalone effects of two NIBS modalities on the PFC through a working memory task, single photon emission computed tomography (SPECT), and salivary cortisol. We hypothesize that the combined protocol will provoke greater changes in the collected measures compared to the remining protocols.

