## Material and methods

### Design

We propose a phase-I, randomized, double-blind, within-subjects, full-factorial study design, which is efficient for testing the standalone and combined effects of tDCS and iTBS.

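### The stated 0.85 power is for an omnibus test across the four conditions and does not carry over to the hypothesis that the combination beats each single technique and sham

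*Protocol article*

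**What the plan says.** The Statistical analyses section names the software ("Sample size was calculated using G*Power 3.1 software") but not the test option chosen in it. The effect size is a convention and not an estimate from data: "we estimate a moderate *f* – size effect (0.25"). The other inputs are: "The analysis considered four groups, 4 measurements, correlation between repeated measures of 0.5, alpha of 0.05 and power of 0.85". The result is given as "resulting in a sample size of 28 participants", and then: "Considering possible losses, we estimate recruitment of 30 subjects (120 observations").

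The Design section describes a "randomized, double-blind, within-subjects, full-factorial study design". Under Procedure, every volunteer attends all four stimulation sessions, and the 120 observations are 30 people times 4 sessions.

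The hypothesis in the abstract is comparative: "We hypothesize that the combined protocol will provoke greater changes in the collected measures" than the other protocols. The end of the Introduction names those as each technique alone and sham. The planned test in the Statistical analyses section is an ANOVA with the stimulation condition (called group) as factor. The article names no contrast or interaction as the test of the hypothesis.

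**The concern.** Two things do not fit together.

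- The inputs count four groups and four measurements, but the design has one group of people and four measurements. The number 28 may therefore belong to a different design.
- An omnibus test asks whether the four condition means differ in any way. Active stimulation differing from sham would be enough, with no advantage for the combination. The hypothesis asks whether the combination exceeds each of the three other protocols. Power for the first question is not power for the second.

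The second matters for interpretation. If the combination does not separate from tDCS alone or iTBS alone, a reader of the article would take that as a null result from a trial with 85% power for the question. The Discussion encourages this by saying that the sample lowers the chance of both error types relative to earlier studies.

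**Working it through.** **Inputs from the Statistical analyses section.** f = 0.25, m = 4 measurements, correlation ρ = 0.5, α = 0.05, target power 0.85, k = 4 groups as stated. Assumptions added here: sphericity, two-sided tests, and the mean patterns in step 3.

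**1. Reproducing 28.** For the within-factor test in a repeated-measures ANOVA:

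λ = f²·N·m/(1 − ρ) = 0.0625 × N × 4/0.5 = 0.5N, df1 = m − 1 = 3, df2 = (N − k)(m − 1).

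With k = 4, N must be a multiple of 4:

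- N = 24: λ = 12, df2 = 60, power 0.813
- N = 28: λ = 14, df2 = 72, power 0.878

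So 28 is the first multiple of 4 that reaches 0.85. The other options tried do not give 28: the four-group within-between interaction needs 40, the between-factor test needs 128, and an independent one-way ANOVA needs 204 observations.

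**2. One group, as in the design.** With k = 1, df2 = 3(N − 1):

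- N = 25: 0.835
- N = 26: 0.851
- N = 28: 0.880
- N = 30: 0.904

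The requirement is 26, so 28 and 30 are both enough for the omnibus test under sphericity.

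**3. The stated hypothesis.** f is the SD of the four condition means divided by σ. The article gives no pattern of means, so two patterns are used, each scaled to f = 0.25.

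- *Additive* (0, a, a, 2a): the SD of the means is a/√2, so a = 0.25 × √2 = 0.354σ. The combination exceeds each single technique by 0.354σ and sham by 0.707σ.
- *Combination only* (0, 0, 0, b): the SD of the means is b√3/4 = 0.433b, so b = 0.25/0.433 = 0.577σ against each of the other three.

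The SD of a paired difference is σ√(2(1 − ρ)) = σ, so these are also the paired standardised differences. The interaction contrast (combined − tDCS − iTBS + sham) has SD σ√(4(1 − ρ)) = 1.414σ. In the combination-only pattern its standardised size is 0.577/1.414 = 0.408; in the additive pattern it is zero by construction.

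Single-contrast power is from the noncentral t. Joint power is simulated, so its second decimal is approximate.

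| Two-sided 0.05 | n = 28 | n = 30 |
|---|---|---|
| Additive: combined vs one single technique | 0.44 | 0.47 |
| Additive: combined vs sham | 0.95 | 0.96 |
| Additive: combined beats all three | 0.27 | 0.29 |
| Combination only: combined vs any one other | 0.84 | 0.86 |
| Combination only: combined beats all three | 0.67 | 0.71 |
| Combination only: interaction | 0.55 | 0.58 |

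A search over 400 random mean patterns with f = 0.25 found none with higher joint power at n = 28 than the combination-only pattern.

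**4. Detectable difference.** For 85% power in one paired contrast, the standardised difference must be 0.59 at n = 28 or 0.57 at n = 30.

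**The case against.** **The group count does no harm.** This stands. Correcting it lowers the requirement from 28 to 26. A reader might infer from the mismatch that the trial is too small; for its omnibus ANOVA it is not.

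**The four groups could be four order sequences.** The n-back section speaks of counterbalanced protocols with order as a model term, and a four-sequence crossover would have k = 4 and m = 4. But the article never states the number of sequences, and the Statistical analyses section uses the word group for the stimulation conditions. Under this reading 28 would be right for the omnibus test, and step 3 would be unaffected.

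**The omnibus test is the planned test, so the sample size matches the analysis.** This also stands. One might say that the wrong test was powered; the article does not support that, because an ANOVA on condition is what it plans and its general aim covers standalone as well as combined effects. The gap lies between that test and the stated hypothesis. Follow-up contrasts may well be in a fuller document, and their absence here is no finding. What the article does print is a single power figure beside a hypothesis to which it does not apply.

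**The low figures depend on the reviewer's choices.** This is partly right. The rationale in the article is that tDCS potentiates or biases the effect of iTBS, which is closer to the combination-only pattern, and there a single contrast has 0.84 to 0.86, practically the stated power. A single contrast of the combination against the average of the other three would have 0.84 (additive) to 0.95 (combination only) at n = 28. One-sided tests would raise power to beat all three to about 0.40 and 0.79 at n = 28. The article specifies neither. Requiring all three comparisons to be significant is a literal reading of the hypothesis, not a criterion the article sets.

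**Conclusion.** The concern holds in a limited form. The 28 is correctly computed for the inputs given, but those inputs describe four groups where the design has one; the effect is two participants on the safe side. The 0.85 is omnibus power only. For the hypothesis as worded, and with the plan's own f and ρ, power at the planned 30 runs from 0.47 to 0.86 for the combination against one single technique, and from about 0.29 to 0.71 for beating all three other protocols.

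These figures assume sphericity, two-sided 0.05 without multiplicity adjustment, no dropout at the stated n, and the two mean patterns, which are not the plan's.

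A reader might infer that true power for the main question is well under half of that claimed. That is not established: half of 0.85 is 0.425, and even the additive single-contrast figure (0.44 at 28) is above it. Only joint significance under the assumed additive pattern falls below.

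**What to change.** Keep 30 participants. In the sample-size paragraph:

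- Redo the calculation with one group and four measurements: 26 needed (0.851), with 0.880 at 28 and 0.904 at 30 under sphericity. If four order sequences were meant, say so.
- Label the result as power for the omnibus test across conditions.
- Add the power, under stated mean patterns, or the detectable paired difference (about 0.59 SD at 28, 0.57 SD at 30 for 85% power) for the combination versus tDCS alone, iTBS alone and sham.
- Add the power for the tDCS-by-iTBS interaction.

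The cost is one paragraph, and a less favourable figure for the main hypothesis than the 0.85 now printed. Enrolment and procedures do not change.

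### A normality pre-test on the sample distribution, not on within-participant residuals, decides between ANOVA and a less powerful rank test; the cost is small with normal data and grows with between-person skew

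*Protocol article*

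**What the plan says.** The Design section describes a "phase-I, randomized, double-blind, within-subjects, full-factorial study design" in which every participant attends all four stimulation sessions.

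The Statistical analyses section sets the analysis rule. It states "The Shapiro-Wilk test will be applied to identify the sample distribution". If the sample is judged normal, the SPECT outcome is compared by ANOVA with group as the factor. Otherwise, "The Kruskal-Wallis test will be performed in case of a non-parametric sample". For the other two outcomes, "ANOVA or its non-parametric extension will be applied for n-back and salivary cortisol"; the rank method is not named there. Residuals are not mentioned, nor is the significance level of the pre-test, nor whether values are pooled or tested by condition.

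The same section bases the sample size on an effect f of 0.25 and on "four groups, 4 measurements, correlation between repeated measures of 0.5, alpha of 0.05 and power of 0.85, resulting in a sample size of 28 participants". It then plans to recruit 30.

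**The concern.** The sample size counts on removing between-person differences: that is what the correlation of 0.5 contributes. A within-participant ANOVA needs roughly normal residuals after the person and condition effects are taken out. It does not need the observed values to be normal across people.

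The pre-test as worded looks at the observed values. These carry the between-person spread, and the four values from one person are correlated, whereas Shapiro-Wilk assumes independent draws. A few people with high levels can make the test reject although the within-participant ANOVA is sound.

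The outcome then moves to a rank test with less power than planned and no effect estimate on the outcome's own scale. Different outcomes could be analysed by different methods, each chosen by its own data.

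**Working it through.** **Inputs from the Statistical analyses section.** f = 0.25, m = 4 measurements, g = 4 groups, correlation ρ = 0.5, alpha = 0.05, power 0.85, N = 28, recruitment 30.

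**Assumed, because the article does not give them.** Pre-test level 0.05; shape of the person levels (normal, gamma with shape 4, log-normal with log-SD 0.5, exponential); normal within-person error.

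**Step 1: reproduce the plan's N.** For a within-participant factor, λ = f²·N·m/(1−ρ), with df1 = m−1 and df2 = (N−g)(m−1).
- g = 4, N = 28: λ = 0.0625 × 28 × 4 / 0.5 = 14, df 3 and 72, power 0.878. This is the smallest N with equal groups that reaches 0.85.
- g = 1, N = 26: λ = 13, df 3 and 75, power 0.851.

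So 28 is reproduced by a repeated-measures calculation. A between-groups calculation needs 128. The planned power therefore belongs to a within-participant ANOVA.

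**Step 2: simulate the rule.** Value = √0.5 × person level + √0.5 × normal error + condition effect scaled to f = 0.25; 2,000 trials per row. The first three result columns are Shapiro-Wilk rejection rates, the next three the power of each test, and the last the overall power of the rule (pooled pre-test, Kruskal-Wallis fallback).

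| N, person level | Pooled values | Any of 4 conditions | Residuals | RM ANOVA | Friedman | Kruskal-Wallis | Rule |
|---|---|---|---|---|---|---|---|
| 28 normal | 0.082 | 0.181 | 0.041 | 0.884 | 0.770 | 0.472 | 0.848 |
| 28 gamma | 0.208 | 0.308 | 0.046 | 0.878 | 0.765 | 0.501 | 0.786 |
| 28 log-normal | 0.339 | 0.436 | 0.038 | 0.882 | 0.778 | 0.562 | 0.762 |
| 28 exponential | 0.426 | 0.497 | 0.044 | 0.890 | 0.786 | 0.581 | 0.735 |
| 30 normal | 0.058 | 0.197 | 0.045 | 0.906 | 0.797 | 0.516 | 0.882 |
| 30 gamma | 0.219 | 0.312 | 0.040 | 0.905 | 0.800 | 0.542 | 0.808 |
| 30 log-normal | 0.363 | 0.440 | 0.038 | 0.888 | 0.780 | 0.588 | 0.758 |
| 30 exponential | 0.456 | 0.530 | 0.042 | 0.906 | 0.804 | 0.610 | 0.748 |

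The Monte Carlo standard error is at most √(0.5 × 0.5 / 2,000) = 0.011, so separate runs differ in the second decimal. Taken over the runs, Friedman lies at about 0.77 to 0.82 and Kruskal-Wallis at about 0.46 to 0.60.

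**Step 3: see where overall power comes from.** Overall power ≈ (1 − rejection rate) × ANOVA power + rejection rate × rank-test power when the pre-test rejects. With 4,000 trials at N = 30 and Kruskal-Wallis as fallback:
- Normal: 0.932 × 0.906 + 0.068 × 0.467 = 0.844 + 0.032 = 0.876 (simulated 0.871).
- Exponential: 0.552 × 0.906 + 0.448 × 0.548 = 0.500 + 0.246 = 0.746 (simulated 0.743).

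In the same runs a Friedman fallback gives 0.888 (normal), 0.862 (log-normal) and 0.848 (exponential). Testing residuals with a Friedman fallback gives 0.893, 0.901 and 0.892.

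**Step 4: false positives.** With no effect at N = 28, the rule with Kruskal-Wallis rejects in 0.042 (normal) and 0.030 (exponential) of trials. Kruskal-Wallis alone rejects in 0.002 and 0.009, because it ignores the pairing. Type I error is not inflated.

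**The case against.** **The loss is modest on the plan's own assumptions.** A reader might infer that the pre-test often rejects and that the trial therefore misses 0.85. The document does not support this. With normal data the pooled test rejects in at most about 8%, and with a Friedman fallback overall power at N = 30 stays at about 0.85 to 0.90 even with exponential person levels. Frequent rejection needs skew that the article does not give. This stands, so the claim is conditional.

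**Most of the loss comes from an unpaired fallback.** Kruskal-Wallis treats four values from one person as independent, and that costs more than the pre-test does. This also stands. But repairing the fallback leaves a pre-test aimed at the wrong quantity and a rank test still below 0.85.

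**The ANOVA is not called repeated-measures.** For a one-way ANOVA by group, testing values by condition would match the model. But that ANOVA has power of only about 0.51 at N = 28, and the sample size shows that a within-participant analysis was meant.

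**A strongly skewed outcome might seem to show a larger cost.** For a log-normal outcome with an assumed log-SD of 0.6, the pre-test fires in over 99% of trials. Yet the raw-scale residuals also fail in about 88%. In one run, raw-scale repeated-measures ANOVA had power 0.82, Friedman 0.80 and log-scale ANOVA 0.89. The switch to ranks costs 0.82 − 0.80 = 0.02; the rest comes from not transforming.

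**Losing the tDCS-by-iTBS term might be blamed on the pre-test.** The ANOVA branch as worded has only group as a factor, so it lacks that term too. The learning check is also planned separately, by session order.

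**An article condenses.** Pooled or per-condition testing may be settled in a fuller document, so both are shown above. The rule itself is stated, and as worded it does not fit the design.

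**Conclusion.** The point holds as a conditional one. The stated rule tests the sample distribution where the within-participant analysis depends on residuals, so between-person differences alone can send an outcome to a rank test.

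If the data are normal, the cost is small: overall power at N = 30 is about 0.87 to 0.88 with Kruskal-Wallis under the pooled pre-test. If person levels are skewed, it falls to about 0.75 to 0.81 with Kruskal-Wallis, and to about 0.85 with Friedman in the most skewed case. These figures rest on f = 0.25, correlation 0.5, a pre-test at 0.05, normal within-person error and assumed person-level shapes. The Kruskal-Wallis figures are certain to apply only to SPECT, since the rank method for n-back and cortisol is not named. The cost is in power and interpretability, not in false positives.

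**What to change.** - Delete the Shapiro-Wilk step as a rule for choosing the test.
- Fix one within-participant model per outcome in advance, with tDCS, iTBS, their interaction and session order.
- Judge normality on that model's residuals, for example with a Q-Q plot.
- Keep a rank test for related samples, such as Friedman in place of Kruskal-Wallis, as a sensitivity analysis only.
- Use a log scale only for an outcome analysed as a strictly positive level, for example post-session cortisol with log pre-session cortisol as covariate. Do not prescribe it across the board: the Abstract defines the cortisol outcome as a change, and the working memory section allows negative response times.

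The cost is a change of wording; no new data are needed. The one downside is that any log-scale outcome is reported as a ratio.

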### Procedure

At the beginning of the study, participants will be screened for participation and asked to give written informed consent. The study is in accordance with the Declaration of Helsinki and was approved by the Ethics Committee at the São Paulo University Hospital das Clínicas (HCFMUSP) and registered on the Plataforma Brasil database (CAAE: 89310918.8.0000.0068).

Participants will be randomized in accordance with a computer-generated list at www.randomizer.org and allocation will be conducted by an assistant not involved in the project. Participants will be asked to come to the research center five times. In line with previous studies of (non)combined NIBS protocols, there will be a one-week interval between the sessions to ensure elimination of carryover effects.^20^ On the first day, all participants will undergo a 3 Tesla MRI (GE, 750W system integrated within a 3.0 Tesla General Electric PET/MRI scanner) scan during which we will acquire T1-weighted and T2-weighted sequences (repetition time [RT] = 1900 ms, echo time [ET] = 2.2 ms, flip angle = 9°, 176 slices/volume, slice thickness = 0.8 mm). MRI acquisition is performed beforehand to target the right and left DLPFC via a neuronavigation system (Brainsight, Rogue Resolutions, Inc). Both left and right DLPFC will be located in each participant by reverse coregistration from the MNI152 stereotaxic coordinates (x - 38, y + 44, z + 26 and x + 38, y + 44, z + 26, respectively) and marked on a cap. This method has been identified as optimal on the basis of clinical outcomes and whole brain functional connectivity.^30 , 31^ After neuronavigation, all other sessions will take place in a well-controlled laboratory environment at the Institute of Psychiatry - HCFMUSP, São Paulo, Brazil. The same procedures will be applied in each of the four sessions, except for neuronavigation, which will only be conducted during the first session.

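### The planned ANOVA is never identified as repeated-measures, and the named fallback, Kruskal-Wallis, is an independent-samples test, although every participant receives all four conditions and the trial was sized on paired data.

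*Protocol article*

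**What the plan says.** **Design.** The Design section states: "We propose a phase-I, randomized, double-blind, within-subjects, full-factorial study design". The Abstract lists four sessions, one for each combination of active or sham tDCS with active or sham iTBS. The Procedure section confirms that each person goes through all of them: "The same procedures will be applied in each of the four sessions", apart from neuronavigation. Thirty people therefore give 120 observations.

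**Sample size.** The Statistical analyses section takes a moderate effect, f = 0.25, and uses "four groups, 4 measurements, correlation between repeated measures of 0.5, alpha of 0.05 and power of 0.85". It arrives at 28 participants and recruits 30.

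**Analysis of SPECT.** After a Shapiro-Wilk test on the sample distribution, the left-DLPFC measure goes into an ANOVA with group as the independent variable. Otherwise: "The Kruskal-Wallis test will be performed in case of a non-parametric sample".

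**Analysis of the other outcomes.** "ANOVA or its non-parametric extension will be applied for n-back and salivary cortisol", again with group as independent variable. For tolerability, "ANOVA will also be applied to investigate adverse effects (dependent variable) across groups (independent variable").

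**What else bears on the model.** The n-back section says that order will be introduced as a variable in the statistical models. No section names a repeated-measures ANOVA, a mixed model, a participant term, the Friedman test or any other paired test.

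**The concern.** In this design the four groups are the same people measured four times. A test that treats the 120 observations as four independent samples leaves the differences between people in the error term. The comparison of conditions does not contain those differences, because they cancel within each person. The error term is then too large for the contrast it judges, and the test rejects too rarely.

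The study's hypothesis is that the combined protocol produces greater changes than either technique alone or sham. The likely harm is a missed effect that is then reported as no added benefit. The plan would also lose the main statistical advantage of a within-subject design, which is what its sample size pays for. The Shapiro-Wilk step does not help: on the unpaired reading, neither branch accounts for the participant.

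**Working it through.** **Inputs.** From the Statistical analyses section: f = 0.25, m = 4 measurements, k = 4 groups, ρ = 0.5, α = 0.05, target power 0.85, N = 28 (30 recruited). Assumed, because not stated: sphericity (ε = 1), compound symmetry and normal data with total variance σ².

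**Step 1: reproduce the plan's 28.** For a repeated-measures ANOVA, within factor:

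- λ = f²·N·m/(1 − ρ) = 0.0625 × 28 × 4 / 0.5 = 14
- df1 = m − 1 = 3; df2 = (N − k)(m − 1) = 24 × 3 = 72
- power = 0.878

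With k = 4 and N a multiple of 4, N = 24 gives 0.813, so 28 is the smallest size that reaches 0.85. With k = 1, N = 28 gives 0.880. The alternatives do not give 28:

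| Calculation | Size needed for power 0.85 |
|---|---|
| Repeated measures, within factor (k = 4) | 28 |
| Within-between interaction | 40 |
| Between factor | 128 |
| Independent one-way ANOVA | 51 per group |

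The trial was therefore sized for a paired test.

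**Step 2: why the unpaired test loses power.** With N = 28 and ρ = 0.5, the expected mean square between conditions is (1 − ρ)σ² + N·m·f²σ²/3 = 0.5σ² + (28 × 4 × 0.0625/3)σ² = 0.5σ² + 2.33σ² = 2.83σ².

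- Unpaired: the error mean square has expectation σ². The ratio is about 2.83, against a 5% critical value F(3, 108) of 2.69. The statistic sits close to its threshold, so power is near one half.
- Paired: the error mean square has expectation (1 − ρ)σ² = 0.5σ². The ratio is about 2.83/0.5 = 5.67, against F(3, 81) = 2.72.

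Under the null the unpaired ratio is about 0.5 rather than 1, which is why the test becomes conservative.

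**Step 3: simulation.** 20,000 trials per setting, with three patterns of condition means, each scaled to f = 0.25:

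| N | ρ | One-way ANOVA | Repeated-measures ANOVA | Kruskal-Wallis | Friedman |
|---|---|---|---|---|---|
| 28 | 0.5 | 0.50 | 0.88 | 0.47 | 0.76 |
| 30 | 0.5 | 0.55 | 0.90 | 0.52 | 0.80 |
| 28 | 0.3 | 0.54 | 0.74 | – | – |
| 28 | 0.7 | 0.46 | 0.99 | – | – |

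Values vary by about 0.01 between mean patterns and runs. With no true effect at ρ = 0.5, the unpaired tests reject in about 0.002 to 0.003 of trials instead of 0.05, while the paired tests stay near 0.05.

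**The case against.** The strongest objection is that the article never calls the ANOVA one-way or between-group. Group is its word for condition, the design is repeatedly called within-subjects, and the sample size uses a repeated-measures correlation. A journal article may shorten repeated-measures ANOVA to ANOVA. This stands as far as it goes: the unpaired ANOVA is an inference. But the rank counterpart of a repeated-measures ANOVA is Friedman, and the counterpart actually named is Kruskal-Wallis. That supports the unpaired reading and is itself an explicit error, not a detail left to a fuller document.

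Other points that stand:

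- Kruskal-Wallis is named only for the SPECT measure. For n-back and cortisol the non-parametric test is unnamed, and adverse effects have no stated fallback.
- Group is not the only model variable, because the n-back section adds order. Order adjusts for learning, however, and does not remove differences between people.
- The SPM step speaks of subtracting images, which is compatible with within-person differences. No unpaired SPM model is specified.
- The gap depends on ρ, which may differ by outcome. It narrows at 0.3 and widens at 0.7.
- The error is conservative, so no excess of false positives follows.

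A reader might go further and infer that confidence intervals will be too wide, or that lost sensitivity on adverse effects will pass for good tolerability. The documents do not support either. No confidence intervals are described, and the simulation uses normal data, whereas the adverse-effect scale is ordinal with four levels. The size of any loss there is not known.

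**Conclusion.** The concern holds in this form: the plan names an independent-samples fallback for a within-subject design, leaves the ANOVA unidentified as repeated-measures, and so does not match the basis of its own sample size. The Kruskal-Wallis error is explicit. For the ANOVA the text is ambiguous and leans towards the unpaired reading.

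The cost is conditional on the tests being run unpaired. At f = 0.25 and ρ = 0.5 the ANOVA loses 0.88 − 0.50 = 0.38 of power at n = 28, or 0.90 − 0.55 = 0.35 if all 30 complete. At n = 28 the loss is 0.74 − 0.54 = 0.20 at ρ = 0.3 and 0.99 − 0.46 = 0.53 at ρ = 0.7. These figures assume normal data, compound symmetry and complete follow-up. It would be too strong to say that the trial will have a power of 0.50, because the article does not establish that the ANOVA is unpaired. Since the wording covers all the main outcomes and the remedy is cheap, it should be corrected before analysis.

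**What to change.** - State the main model as a repeated-measures ANOVA or, preferably, a linear mixed model with participant as random effect and tDCS, iTBS, their interaction and session order as fixed effects. This keeps the order adjustment already planned and uses the full-factorial structure.
- Check the distribution of model residuals rather than of the raw sample.
- Replace Kruskal-Wallis with Friedman or a within-participant permutation test, and name the same fallback for n-back and cortisol.
- Analyse adverse-effect scores with a paired ordinal method.
- State that the SPM model includes a subject factor.

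The cost is wording and slightly more analysis work. The data and the number of participants do not change.
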